#### Secondary efficacy outcomes

Key secondary efficacy measures at 24 months will include:Mean change in serum levels or titres of antibodies to HNPs or leiomodin and serum levels or titres of inflammatory markers.Mean change in dermal microfilaria density on real time PCR at 24 months.The proportions of patients achieving seizure freedom (≥1 month without head nodding or convulsive seizures), mean change in Cogstate scores, the proportions of patients with inter ictal epileptiform discharges on diagnostic EEG, proportion of participants with Gross Motor Function Classification System (GMFCS) scores 3–5; and the proportion of participants with mental health disorders on the MINI-KID and intellectual disability on the CAIDS-Q and the proportion of participants with improved Quality of Life.Others will be mean changes in weight-for-age, height-for-age (stunting), and height-for-weight (wasting) Z-scores and proportions of participants with wasting and stunting (Z-scores <− 3 SD)Incidence rate of non-nodding syndrome sick clinic visits and all cause sick clinic visits; incidence rate of all-cause hospital admissions and all-cause mortality

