**Methods:**

This will be a two-arm, double-blind, placebo-controlled, randomised phase II trial of doxycycline 100 mg daily for six weeks in 230 participants. Participants will be patients’ ages≥8 years with nodding syndrome. They will receive standard of care supportive treatment. All will be hospitalised for 1–2 weeks during which time baseline measurements including clinical assessments, EEG, cognitive and laboratory testing will be performed and antiepileptic drug doses rationalised. Participants will then be randomised to either oral doxycycline (Azudox®, Kampala Pharmaceutical Industries) 100 mg daily or placebo. Treatment will be initiated in hospital and continued at home. Participants will be visited at home at 2, 4 and 6 weeks for adherence monitoring. Study outcomes will be assessed at 6, 12, 18 and 24-month visits. Analysis will be by intention to treat. The primary efficacy outcome measure will be the proportion of patients testing positive and the levels or titires of antibodies to host neuron proteins (HNPs) and/or leiomodin at 24 months. Secondary outcome measures will include effect of the intervention on seizure control, inflammatory markers, cognitive function, disease severity and quality of life.

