### Follow period and study outcome determination

Study participants will be re-evaluated at 6, 12, 18 and 24 months. Only clinical assessments will be performed at 6, 12 and 18 months. At 24 months, however, participants will again be hospitalised for one week for inpatient observation and testing, during which all the pre-randomisation procedures and tests will be repeated to determine study outcomes.

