### Statistical analysis

Analysis will be by intention to treat. The analysis will compare the proportions of patients testing positive for and the levels or titres of antibodies to HNPs or leiomodin at baseline and at 24 months in both arms. Both crude (unadjusted) and adjusted effect estimates will be computed. The chi square test will be used to compare proportions of children with the different antibodies in the two arms; the Students t-test will be used for means of normally distributed data and the Mann-Whitney U test for skewed data. We will also determine the mean change or reduction in the levels or titres of the antibodies and inflammatory markers with the intervention. Time to event (e.g. to seizure resolution) will be measured from the date of randomisation using Kaplan Meyer Survival analysis and by Cox regression analysis. For the cognitive tests, in addition to classification as impaired or not (in comparison to norms determined from unaffected sibling controls in the concurrent case control study), we will also measure mean improvements in scores. The rates determined will be adjusted for age, HIV infection, weight for height z scores and corrected for multiple testing. We will examine safety (serious adverse events and adverse events) and assess compliance and the factors for poor compliance.

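### For clinical outcomes recorded at all four follow-up visits, the month-24 comparison is planned without the earlier readings, which would guard it against bias from outcome-related loss

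*Protocol article*

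**What the plan says.** The abstract's Methods paragraph states: "Study outcomes will be assessed at 6, 12, 18 and 24-month visits". The section on follow-up and outcome determination narrows this: "Only clinical assessments will be performed at 6, 12 and 18 months". At month 24 participants are readmitted, "during which all the pre-randomisation procedures and tests will be repeated to determine study outcomes".

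The section Secondary efficacy outcomes opens with "Key secondary efficacy measures at 24 months will include". Its list includes the proportion seizure-free, GMFCS grade and growth Z-scores. It also includes outcomes that accrue over time, such as "incidence rate of all-cause hospital admissions and all-cause mortality".

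Statistical analysis says "Analysis will be by intention to treat". It assigns the chi-square test to antibody proportions, and for continuous data "the Students t-test will be used for means of normally distributed data and the Mann-Whitney U test for skewed data". It adds: "Time to event (e.g. to seizure resolution) will be measured from the date of randomisation using Kaplan Meyer Survival analysis and by Cox regression analysis". It promises crude and adjusted estimates but names no analysis that combines repeated visits.

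**The concern.** Seizure status is a clinical reading that the interim visits can supply. GMFCS and anthropometry probably are too, although the article does not list what those visits contain. For these outcomes the plan fixes both the time point (month 24) and a set of single-time-point tests. A participant seen at 6, 12 and 18 months but not at 24 then adds nothing to the proportion seizure-free unless the missing value is imputed.

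These outcomes show whether patients benefit, and the sample size was set on antibodies only. A comparison restricted to participants with a month-24 value is unbiased only if loss is unrelated to outcome. Families of children who do badly, or who recover, may well leave at different rates in the two arms. The earlier visits hold the information needed to correct for this.

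**Working it through.** **1. The plan's own figure.** Inputs from Sample size: 50% v 30%, 80% power, 5% level (two-sided assumed), 10% loss. With p̄ = 0.40:

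n = [1.960·√(2·0.40·0.60) + 0.842·√(0.50·0.50 + 0.30·0.70)]² / 0.20² = 93 per arm.

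Continuity correction: (93/4)·[1 + √(1 + 4/(93·0.20))]² = 103 per arm. Then 103/0.9 = 114.4, rounded up to 115 per arm, or 230. This reproduces the stated figure. The sizing therefore already treats lost participants as adding nothing to the antibody comparison. No stated number is wrong.

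**2. Which outcomes have earlier readings.**

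| Outcome | Readings after randomisation | Affected? |
|---|---|---|
| Antibodies, inflammatory markers, skin snips, EEG | month 24 only | no |
| Cogstate, MINI-KID, CAIDS-Q, QOLCE | month 24; interim use not stated | no |
| Sick visits, admissions, mortality, adverse events | accrue over follow-up | no |
| Time to seizure resolution | from randomisation | no |
| Proportion seizure-free at month 24 | clinical visits at 6, 12, 18, 24 | yes |
| GMFCS, growth Z-scores at month 24 | same, if recorded there | probably |

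**3. Power gained for the month-24 contrast.** The documents give no between-visit correlation, so ρ is assumed. With N = 115 per arm, loss d = 0.10 and one earlier visit correlated ρ with month 24, the effective number per arm is

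N / [(1 − ρ²)/(1 − d) + ρ²].

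Power = Φ{[Δ√n − 1.960·√(2p̄(1 − p̄))] / √(p₁(1 − p₁) + p₂(1 − p₂))}, without continuity correction. The pair 50% v 30% is the protocol's own; 30% v 45% is an assumed seizure-freedom effect.

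| | n per arm | power, 50% v 30% | power, 30% v 45% |
|---|---|---|---|
| Completers only | 103.5 | 84.1% | 60.7% |
| ρ = 0.3 | 104.4 | 84.4% | 61.1% |
| ρ = 0.5 | 106.2 | 85.0% | 61.8% |
| ρ = 0.7 | 108.8 | 85.9% | 62.9% |
| ρ = 0.9 | 112.6 | 87.0% | 64.4% |

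The gain is 0.3 to 2.9 points in the first case and 0.4 to 3.7 in the second. Even with no loss at all (n = 115), power would be only 87.7% and 65.3%.

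**4. Bias from outcome-related loss.** Assumptions: seizure-free 30% (placebo) and 45% (doxycycline) at both month 18 and month 24; latent-normal correlation r between the two; all loss after month 18. In the placebo arm 12% of those not seizure-free and 5% of those seizure-free are lost. In the doxycycline arm 15% of those seizure-free and 5% of the others are lost.

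For r = 0.5, the chance of being seizure-free at month 24 is 0.523 (placebo) and 0.633 (doxycycline) for those free at month 18, and 0.205 and 0.300 for those not free.

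- Placebo completers: (0.30·0.95·0.523 + 0.70·0.88·0.205)/0.901 = 0.305; loss 9.9%.
- Doxycycline completers: (0.45·0.85·0.633 + 0.55·0.95·0.300)/0.905 = 0.441; loss 9.5%.
- Completer difference: 13.6 points. For r = 0.7 it is 12.9, and for r = 0.85 it is 12.2.

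Reweighting by month-18 status gives 0.30·0.523 + 0.70·0.205 = 0.30 and 0.45·0.633 + 0.55·0.300 = 0.45, so the true 15 points return.

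**5. The 18/24-month average.** With equal variances, the mean of two visits has (1 + r)/2 times the variance of one visit: 0.70 to 0.85 for r = 0.4 to 0.7. In simulations with 30% v 45%, 115 per arm and 10% loss, its power was about 70–81% if the effect is constant and 61–72% if it builds up over the visits (3, 8, 12, 15 points). Month 24 alone gave about 60–64%. This is a different quantity from the month-24 contrast, so its gain cannot be credited to the main fix.

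**The case against.** A reader might infer that the secondary comparisons rest on the month-24 visit alone, that the interim data are thrown away, and that everyone lost before month 24 is excluded from an analysis called intention to treat. The article does not support this.

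- Kaplan-Meier and Cox analyses run from randomisation, with seizure resolution as the example. The incidence-rate outcomes and adverse events accrue over follow-up. In these analyses an early leaver contributes until loss. The 12-month interim analysis, aimed particularly at seizure control, also uses earlier data.
- Exclusion of early leavers is stated nowhere. The article is silent on missing month-24 values, and that is commonly left to the analysis plan, which is not shown.
- The chi-square test is worded for antibodies. No test is tied by name to seizure freedom or GMFCS.
- A month-24 endpoint is a legitimate choice, matches the primary time point and does not contradict intention to treat.

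All of this stands, and it limits the point to a few outcomes. It does not remove it. Time to first resolution is not the same as status at month 24, since seizure freedom can be lost again, and it says nothing about GMFCS or growth. The interim analysis is a stopping look, not a final comparison. Adjusting for age, HIV and weight-for-height does not bring in the earlier visits.

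**Conclusion.** The point holds in a narrow form. For seizure freedom, and for GMFCS and growth if recorded at the interim visits, the plan fixes the comparison at month 24 and names only single-time-point tests. Apart from the time-to-event analysis, no stated final comparison uses the earlier readings of these outcomes.

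The power at stake is small. The reason to change is robustness: a shortfall of about 1.4 to 2.8 points on a true 15 under the loss pattern assumed above. That pattern is illustrative. Another could inflate the difference, and loss unrelated to outcome would leave it unbiased. The correction works only as far as the earlier visits explain the loss. The weight of the point is modest, and an unseen analysis plan may already settle it.

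**What to change.** Keep month 24 as the outcome. For clinical outcomes recorded at all four visits, state that the month-24 arm contrast will be estimated as follows:

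- **Continuous scores:** a likelihood-based mixed model with arm, visit and arm-by-visit.
- **Yes/no outcomes:** multiple imputation from the earlier visits, weighted GEE, or a likelihood-based logistic mixed model. Ordinary unweighted GEE is not enough, because it generally needs loss to be completely at random. With an independence working correlation and full arm-by-visit terms it simply returns the completer comparison.

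An average of the month-18 and month-24 contrasts may be added as supportive only, since it describes a period. Averaging all four visits should not lead, because it loses power if the effect builds up slowly. State which clinical measures are taken at the interim visits.

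Leave unchanged the outcomes measured only at month 24, the tests not stated to be done at interim visits, and the time-to-event and incidence-rate analyses.

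The cost is analysis wording, slightly more programming and reliance on a model for missing values. No visits or tests are added.

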### Sample size

From our pilot studies, ~ 50% of patients with prevalent nodding syndrome had antibodies to a HNPs and ~ 60% to leiomodin [2, 22]. We hypothesise that among patients with new onset nodding syndrome (symptoms < 12 months), six weeks’ therapy with doxycycline will cause a 50% reduction in the proportion of patients with and the levels or titres of antibodies to HNPs (a reduction from 50 to 25% compared to placebo) at 24 months. In Uganda, however, there has been no incident cases of nodding syndrome since 2014. It is anticipated that the intervention may not be as efficacious in patients with established symptoms (i.e. patients with symptoms ≥12 months) and the effect on antibodies would be smaller (an anticipated 40% reduction from 50 to 30%). To demonstrate this effect at 80% power and 5% level of significance and allowing for 10% losses to follow up, we will need to recruit a total of 230 patients with established symptoms (115 in either arm).

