### Randomisation, allocation and treatment initiation phase

Once all pre-randomisation assessments are complete, participants will be randomised to either doxycycline or placebo with a 1:1 allocation as per a computer-generated randomisation schedule stratified by skin snip test results in to four groups; A, B, C and D. The randomisation code and stratification will be prepared by an independent statistician at a data centre at Global Health Uganda. The study pharmacy assistant will email the independent data centre with the study ID and the microscopy results of the skin snip for *O.volvulus* and the data centre statistician will allocate the participant to the study arms*.*

Eligibility criteria for randomisation are fulfilment of the enrolment criteria and the dose of sodium valproate rationalised to at least 20 mg/kg/day (maximum 35 mg/kg/day) if the patient still experiences one or more tonic clonic seizures a month. Participants reported to be unable to swallow capsules, those already enrolled (or who will enrol) into another trial, and those who withdrew consent since enrolment, will be excluded from randomisation.

The intervention drugs (doxycycline capsules [Azudox®] and placebo) will be obtained from Kampala Pharmaceutical Industries, Uganda. The active drug and the placebo will be labelled with the study code by Kampala Pharmaceutical Industries in collaboration with the independent statistician. Each Azudox capsule contains doxycycline hyclate equivalent to 100 mg of doxycycline base. In the treatment of *Onchocerca volvulus,* doxycycline is given in doses of 100-200 mg/day for 4–6 weeks [31]. We chose the lower dose of 100 mg/day since most participants will be adolescents many of who will also have wasting. With an average weight of 33 kg, we anticipate this dose will translate to ~ 3 mg/kg/day. The two interventions will be identical in the number of capsules (one) per day and timing. The drug administration procedures will also be identical. Both the caretakers and investigators will be blinded. However, in the event of medical emergency un-blinding of an individual participant to the PI or safety monitoring teams may be conducted. Otherwise, all treatment allocations will only be disclosed after the data is locked and a statistical analysis plan is in place.

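### Four yes/no secondary outcomes are 24-month proportions, and the named covariates omit each participant's own recorded baseline status, which costs precision and power but not validity

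*Protocol article*

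**What the plan says.** All references are to the protocol article.

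- **Secondary efficacy outcomes** lists, among the key measures at 24 months, "the proportions of patients with inter ictal epileptiform discharges on diagnostic EEG", the proportion with GMFCS scores 3-5, and "the proportion of participants with mental health disorders on the MINI-KID and intellectual disability on the CAIDS-Q". None of these four refers to the starting state. In the same list, antibody levels, microfilaria density, Cogstate and the anthropometric Z-scores are defined as mean changes, and quality of life as improved. Wasting and stunting also appear as proportions.
- **Inpatient assessment** places EEG (explicitly for all), GMFCS, MINI-KID, CAIDS-Q and nutritional status before randomisation.
- **Follow period and study outcome determination** says that at 24 months "all the pre-randomisation procedures and tests will be repeated to determine study outcomes". Status at entry and at month 24 can therefore be paired for each participant.
- **Statistical analysis** promises both crude and adjusted estimates, then states: "The rates determined will be adjusted for age, HIV infection, weight for height z scores and corrected for multiple testing". The chi-square sentence in that section concerns antibody proportions. No test is named for the four outcomes discussed here.
- **Randomisation, allocation and treatment initiation phase** stratifies by skin snip result only, so the design does not balance these four states.

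**The concern.** The article's Discussion says the trial has to rely on patients with established symptoms and expects lower degrees of improvement. Many participants may therefore enter with epileptiform discharges, motor impairment, a psychiatric disorder or intellectual disability, and many may still have it two years later. The 24-month prevalence then largely reflects who was affected at entry. Chance differences between arms at entry pass into the 24-month difference as noise, and remission and new onset are merged into one figure.

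The outcome's own baseline value is plausibly its strongest predictor, and the trial already collects it. Naming three other covariates and leaving this one out gives up precision on the outcomes that carry much of the clinical evidence, in a trial sized for antibodies.

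**Working it through.** **1. Evaluable numbers.** Inputs from Sample size: "To demonstrate this effect at 80% power and 5% level of significance and allowing for 10% losses to follow up", "an anticipated 40% reduction from 50 to 30"%, and "230 patients with established symptoms (115 in either arm"). From Randomisation: "randomised to either doxycycline or placebo with a 1:1 allocation".

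Two-sided comparison of 0.50 with 0.30, pooled proportion 0.40:

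n = [1.960 × √(2 × 0.40 × 0.60) + 0.842 × √(0.50 × 0.50 + 0.30 × 0.70)]² / 0.20² = 93.0 per arm.

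With continuity correction: (93.0/4) × [1 + √(1 + 4/(93.0 × 0.20))]² = 102.8, so 103 per arm. Then 103/0.90 = 114.4, so 115 per arm and 230 in total. The stated figure is reproduced. It was derived for the antibody outcome, not for the outcomes discussed here. The calculations below use 103 per arm.

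**2. Chance imbalance at entry.** SE of the baseline difference = √(2p(1−p)/103).

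| Baseline prevalence p (assumed) | SE, points | 95% range, points | P(gap ≥ 10 points) |
|---|---|---|---|
| 20% | 5.6 | ±10.9 | 7% |
| 30% | 6.4 | ±12.5 | 12% |
| 50% | 7.0 | ±13.7 | 15% |

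If φ is the correlation between baseline and 24-month status, and prevalences are similar at both times, about φ times the gap carries into the 24-month difference. For example, a 10-point gap with φ = 0.7 contributes about 7 points.

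**3. Power with and without baseline status, normal approximation.** Adjustment multiplies the variance by (1 − φ²), so power = Φ(d / [SE × √(1 − φ²)] − 1.96), with SE = √{[p₁(1−p₁) + p₂(1−p₂)]/103}. The document gives no prevalence, effect or φ for these outcomes, so all are assumed.

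- 50% v 35%: SE = 0.0681, d/SE = 2.203.
- 50% v 40%: SE = 0.0690, d/SE = 1.450.

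| φ | Variance reduction | 50% v 35% | 50% v 40% | 206 patients act like |
|---|---|---|---|---|
| crude | – | 59.6% | 30.5% | 206 |
| 0.3 | 9% | 63.7% | 33.0% | 226 |
| 0.5 | 25% | 72.0% | 38.7% | 275 |
| 0.6 | 36% | 78.6% | 44.1% | 322 |
| 0.7 | 49% | 87.0% | 52.8% | 404 |

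A simulation with baseline status as a linear covariate (20,000 trials per setting) agreed. At 50% v 35%, crude power was about 60%, and adjusted power was 62.6%, 71.6% and 78.5% at φ = 0.3, 0.5 and 0.6.

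**4. Power under explicit persistence.** Simulated trials at 103 per arm compare a crude chi-square with a Mantel-Haenszel test stratified by baseline status. Persistence is the chance that a state present at entry is still present at month 24. Each pair is placebo v doxycycline.

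| Baseline | Persistence | New onset | Crude | Stratified |
|---|---|---|---|---|
| 50% | 90% v 75% | 10% v 5% | 31% | 60% |
| 70% | 95% v 85% | 20% v 10% | 34% | 63% |
| 30% | 85% v 65% | 10% v 5% | 34% | 56% |
| 50% | 75% v 60% | 25% v 15% | 45% | 54% |

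The first three rows imply φ of about 0.65 to 0.80. The fourth implies about 0.5.

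**5. Type I error.** With no treatment effect, both the crude and the baseline-adjusted tests rejected in about 5% of trials.

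**The case against.** A reader might infer three stronger things, none of which the document supports.

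- **That these outcomes will be compared only as raw prevalences.** Statistical analysis promises adjusted estimates as well as crude ones. What can be said is that baseline status is not among the named covariates. It is also unclear whether the covariate sentence covers these outcomes, because it directly follows the sentence on cognitive tests.
- **That a chi-square test is laid down for them.** That sentence is about antibody proportions. The crude test used above is only a reference for an analysis without baseline status.
- **That chance imbalance biases the result or produces extra false positives.** Under randomisation the 24-month comparison is unbiased, and the 5% level already allows for chance imbalance.

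Two further objections have weight. First, covariates for secondary outcomes are often left to the analysis plan, which is not shown and may add baseline status. Silence would be no finding, but this article does name a set, and adding a collected baseline value improves a stated method. Second, the size of the gain rests on assumed values, and the first three persistence scenarios are favourable ones. With weak persistence the gain is small. Adjustment also does not rescue outcomes for which the trial was not sized: at 50% v 40%, adjusted power is at most about 60% in the cases examined.

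**Conclusion.** The point holds as a matter of efficiency and interpretability, not validity. Four yes/no outcomes are defined as 24-month proportions, their baseline status is collected, and the stated covariates omit it.

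At 103 per arm, the power given up runs from about 2.5 points (50% v 40%, φ = 0.3) to about 30 points (the strongly persistent scenarios with φ about 0.7 to 0.8). Where each outcome falls in that range cannot be read from the document. Persistent conditions such as intellectual disability or motor impairment plausibly lie towards the upper end, but that is a judgement. In no assumed setting with φ of 0.3 or more did leaving baseline status out give higher power. Because these are secondary outcomes and type I error is intact, the change is worth making but is not critical.

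**What to change.** In Statistical analysis, add each outcome's own baseline status to the covariates for the between-arm comparison at 24 months of EEG discharges, GMFCS 3-5, MINI-KID disorder and CAIDS-Q intellectual disability. Do the same for the wasting and stunting proportions, which have the same form and a baseline assessment. Use either a Mantel-Haenszel test stratified by baseline status, or logistic regression including it with a standardised risk difference. State that the covariate sentence applies to these outcomes. The wording should make clear that arms are compared with each other, given baseline status. It must not be readable as a before-after test within an arm.

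Keep the crude proportions alongside. Tabulate by arm the remissions among those affected at entry and the new onsets among those not affected.

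The cost is wording only, with no new visits or measurements. The one small downside is that a rule is needed for the few participants without a baseline result. The change should be fixed before allocations are disclosed.

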### Inpatient assessment

After eligibility is confirmed and consent obtained, the subject will be hospitalised for 1–2 weeks in Kitgum General Hospital for baseline assessments. The patients’ treatment will be updated per standard of care protocols. The clinical assessment will include a review of the pregnancy, birth and developmental history, the past medical history, a description of the progressive development of the symptoms of nodding syndrome, and the burden and types of seizures. A detailed physical assessment will also be performed including a neurologic, psychiatric and cognitive examination. The Gross Motor Function Classification System (GMFCS) and the Modified Rankin Scale will be used to describe gross motor abilities. The Mini-International Neuropsychiatric Interview for Children and Adolescents (MINI-KID) [26] will be used to document psychiatric disorders and the disorders classified per the Diagnostic Statistical Manual (DSM)-V criteria; Intellectual Disability will be assessed using the Child and Adolescent Intellectual Disability Screening Questionnaire (CAIDS-Q) [27]; nutritional status will be assessed against WHO 2000 anthropometric standards; cognitive function will be assessed using the Cogstate - a computerised cognitive testing program [28], and the quality of life (QOL) will be assessed using the Quality of Life in Childhood Epilepsy (QOLCE) questionnaire [29].

All participants not on standard of care treatments will be initiated on therapy including sodium valproate for seizures, nutritional, physical and psychological therapy as appropriate. Patients receiving current standard of care treatment but with ongoing seizures will have their doses of sodium valproate optimised to 20-35 mg/kg/day.

Five-10mls of blood will be drawn for standard of care testing (full blood count, liver and renal function tests, and HIV). We will also obtain skin snips for *O.volvulus* microfilaria density (on microscopy and Real Time [RT] PCR) and *Wolbachia* load testing. Lumbar puncture will be performed and 3-4mls of cerebrospinal fluid obtained. Aliquots of plasma, serum and cerebrospinal fluid will be stored for baseline evaluation of study specific tests.

All will have a 30-min diagnostic electroencephalographic (EEG) recording. In addition, an overnight EEG will be obtained in a convenient sample of 45 participants selected by stratified random sampling to reflect the five clinical stages of nodding syndrome [30].

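### Quality of life and GMFCS are analysed only as yes/no proportions although both full scales are collected at baseline and 24 months, which costs appreciable power on two secondary outcomes

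*Protocol article*

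**What the plan says.** Under Secondary efficacy outcomes, the protocol article lists among its key 24-month measures "proportion of participants with Gross Motor Function Classification System (GMFCS) scores 3–5" and "the proportion of participants with improved Quality of Life". No other summary of either outcome is given there or under Statistical analysis.

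The fuller data will exist. Under Inpatient assessment, "the quality of life (QOL) will be assessed using the Quality of Life in Childhood Epilepsy (QOLCE) questionnaire", and "The Gross Motor Function Classification System (GMFCS) and the Modified Rankin Scale will be used to describe gross motor abilities". At 24 months participants are readmitted, "during which all the pre-randomisation procedures and tests will be repeated to determine study outcomes".

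Other outcomes in the same list stay on their scale. Cognition is summarised as "mean change in Cogstate scores"; antibody levels, microfilaria density and anthropometric Z-scores are also mean changes. Wasting and stunting are given both ways, as Z-score changes and as proportions. Under Statistical analysis, cognition is classified as impaired or not, but "we will also measure mean improvements in scores" as well. Quality of life and GMFCS have no such second analysis.

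**The concern.** Reducing a score or an ordered scale to two categories discards information. On GMFCS, a participant who moves from level 5 to level 3, or from level 2 to level 1, contributes no change to the listed outcome. On quality of life, a large and a small gain count alike once both qualify as improved, and all who do not qualify are treated as equal.

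The primary outcome is a biomarker, so the clinical secondary outcomes help show whether an antibody effect reaches the patient. The article's Discussion also expects smaller improvements in patients with established symptoms. An inefficient summary makes a modest real benefit easier to miss, in a trial whose size is set by the antibody outcome.

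**Working it through.** **1. The plan's own figure.** The only power statement (Sample size) is for antibody positivity: 50% v 30%, 80% power, 5% significance (taken as two-sided), 10% loss.
- Uncorrected: n = [1.96·√(2·0.4·0.6) + 0.842·√(0.25 + 0.21)]² / 0.20² = 93 per arm.
- With continuity correction: (93/4)·[1 + √(1 + 4/(93·0.20))]² = 103 per arm.
- With loss: 103/0.9 = 114.4, so 115 per arm and 230 in total.

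The stated 230 is reproduced, and 103 evaluable per arm is used below. The plan gives no power, SD, correlation or responder rate for quality of life or GMFCS, so every other input below is an assumption.

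**2. Quality of life.** Assume normal scores, a true effect d = 0.4 SD, a baseline to follow-up correlation r = 0.5, no average change on placebo, and improved meaning a change above zero (so 50% of placebo patients improve).
- SD of change = √(2(1 − r)) = 1.0.
- Proportion improved on doxycycline = Φ(0.4/1.0) = 65.5%. Power for 50% v 65.5% is about **62%**.
- Mean change: Φ(0.4·√(103/2) − 1.96) = Φ(0.91) = **82%**.
- ANCOVA, residual SD = √(1 − r²) = 0.866: Φ((0.4/0.866)·√(103/2) − 1.96) = Φ(1.35) = **91%**.
- Over d = 0.3 to 0.5 and r = 0.4 to 0.6, power is 34–88% as a proportion and 65–99% by ANCOVA.

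**3. Information lost on quality of life.** For a normal score cut at c, with a proportion p beyond the cut, the efficiency relative to the mean is φ(c)²/[p(1 − p)].
- At p = 50% this is 0.637, a loss of 36%. The loss is 42% at 30%, 51% at 20% and 66% at 10%.
- Against ANCOVA, multiply by (1 − r²)/[2(1 − r)] = (1 + r)/2. At r = 0.4, 0.5 and 0.6 the efficiency is 0.45, 0.48 and 0.51, a loss of 49–55%.

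**4. A stricter definition of improved.** Take the effect that gives mean change 80% power with 103 per arm: (1.96 + 0.842)·√(2/103) = 0.39 SD of the change score. Analysed as a proportion:

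| Placebo patients improving | Power | Ratio of miss rates (v 20%) |
|---|---|---|
| 50% | 60% | 2.0 |
| 30% | 59% | 2.1 |
| 20% | 54% | 2.3 |
| 10% | 42% | 2.9 |

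A threshold that few placebo patients reach therefore costs more. At a 50% split, the ratio is 1.3 when mean change has 50% power and 2.8 when it has 90%.

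**5. GMFCS.** Assume a common odds ratio of 2, 103 per arm, and two illustrative placebo distributions over levels 1 to 5. Each was simulated 3,000 times, with a z-test on levels 3–5 v lower and a rank test on all five levels.

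| Placebo distribution (%) | Cut at 3–5 | All five levels | Ratio of miss rates |
|---|---|---|---|
| 35/30/20/10/5 | 62% | 76% | 38/24 = 1.6 |
| 55/25/10/6/4 | 42% | 69% | 58/31 = 1.9 |

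The information lost, 1 − [(1.96 + z for the lower power)/(1.96 + z for the higher power)]², is about 28% and 49%. As an analytic check, q(1 − q) for the cut against (1 − Σp³)/3 for the ordinal scale gives:
- first distribution: 0.2275/0.307 = 0.74, a loss of 26%;
- second distribution: 0.16/0.272 = 0.59, a loss of 41%.

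**The case against.** The strongest reply is that these are secondary outcomes with no power claim, that nothing here is miscalculated or contradictory, and that a proportion is easy to read. Threshold outcomes also occur elsewhere in the list (intellectual disability, severe wasting and stunting). The list is open-ended, the analysis section provides for t-tests and Mann-Whitney tests, and the SAP is not shown. All of this stands, and it limits the weight of the point. It does not remove it: the article names the summary for both outcomes, and an SAP that followed it would compare two proportions.

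A reader might go further in four ways that the documents do not support.
- **Any rise in score counts as improved, so half improve by noise.** The article gives no rule for improvement. A condensed article may leave that to the full protocol or SAP, so its absence is no fault. The 50% used in the working is an assumption.
- **Most of the information is discarded.** For quality of life the loss is about a third against mean change. It reaches about half only against ANCOVA, and part of that is the separate gain from baseline adjustment. The GMFCS loss is about a quarter to a half. A larger loss needs a low responder rate or few patients at levels 3–5, and neither rate is given.
- **The chance of missing an effect doubles.** That holds in some scenarios only, as the ratios in the working show.
- **Little else speaks to patient benefit.** Seizure freedom, Cogstate, psychiatric disorders, intellectual disability, growth, clinic visits, admissions and mortality are all listed.

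**Conclusion.** The point holds as a matter of efficiency. Two outcomes measured in full at both times are listed only as proportions, while similar outcomes in the same list keep their scale, and no reason is given for the difference.

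In the reference case, a real quality-of-life effect would be missed about 38% of the time as a proportion, 18% as mean change and 9% by ANCOVA. For GMFCS the figures are about 38% against 24%, or 58% against 31%. These sizes depend on the assumed effect, correlation, normality, responder rate, proportional odds and level distributions. The direction of the loss holds across the ranges examined; its amount is uncertain. The matter is confined to these two secondary outcomes and does not touch the primary outcome or the 230.

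**What to change.** Make these the main analyses of the two outcomes:
- 24-month QOLCE score compared between arms by ANCOVA with the baseline score as covariate;
- 24-month GMFCS level compared by a proportional-odds model with baseline level as covariate.

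Keep the proportion improved and the proportion at GMFCS levels 3–5 as supportive results, and state the rule for improvement beside the first. The baseline score has to be named as a covariate, because the article's stated adjustments are age, HIV infection and weight-for-height Z-score.

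The cost is a wording change to both the protocol and the SAP, made before unblinding because the article lists the proportions as key secondary measures. A mean difference and a common odds ratio are slightly harder to read than two percentages, which is why the proportions stay. No extra visit, instrument or participant is needed.
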